**Fig. 1 Fig1:**
[figure not shown]
mini-MED clinical trial study design. After a 2-week washout, participants in the mini-MED clinical trial are randomized (1:1) to start one dietary intervention containing 500 kcal/day from target foods, with subsequent assignment to the other upon completion of the first. Each 4-week intervention is repeated once. The mini-MED arm contains target foods found within a Mediterranean-style (MED) dietary pattern and includes a second randomization to first receive either salmon or lean, unprocessed beef as a protein source, with consumption of the alternate protein source during the second mini-MED intervention period. The Western arm contains foods found within a habitual/Western-style (Western) dietary pattern with only lean, unprocessed beef as a protein source. All dietary intervention periods are 4 weeks in duration. Participants complete in-person assessments and data collection pre/post each intervention period (baseline and intervention weeks 4, 8, 12, and 16). Figure created with BioRender.com

## Methods: participants, interventions, and outcomes

### Study setting {9}

This study takes place at a single study site: the University of Colorado Anschutz Medical Campus in Aurora, CO, USA. The study protocol has been approved by the Colorado Multiple Institutional Review Board (COMIRB).

### Eligibility criteria {10}

To be eligible to participate in this research, volunteers must meet the following:

Inclusion criteria:Body mass index between 25 and 37 kg/m^2^ and weight-stable;Age 30–69 years;Nonsmoker (including tobacco, marijuana, and other inhaled substances);Self-reported consistent physical activity levels for 3 months prior to and throughout the study period;Stable medication usage for 6 months prior to and throughout the study period;Having at least one self-reported component of Metabolic Syndrome: i.e., elevated fasting glucose (≥ 100 mg/dL), elevated blood pressure (systolic ≥ 130 and/or diastolic ≥ 85 mmHg), elevated waist circumference (≥ 94 cm in males; ≥ 80 cm in females), elevated triglycerides (≥ 150 mg/dL), and/or reduced HDL cholesterol (< 40 mg/dL in males; < 50 mg/dL in females) OR on medication for the treatment of hyperglycemia, hypertension, or hypercholesterolemia [19];Report of baseline consumption of a habitual dietary pattern not meeting criteria for a Mediterranean-style dietary pattern, defined as a score of ≤ 7 (on a zero to 14 scale of whole numbers) as assessed via the Mediterranean Diet Assessment Tool [20];Follows an omnivorous dietary pattern and willing to consume all provided study foods;Willingness to refrain from consumption of nutritional supplements, herbal supplements, botanical supplements, and pre- or probiotics aside from those prescribed by a physician for the duration of the study;Willingness to come to the University of Colorado Clinical and Translational Research Center (CTRC) monthly for clinical assessments and biospecimen collection;Willingness to participate in telephone interviews and data collections at the midpoint of the intervention periods;No plans to relocate or for extended travel (greater than 1 week) within next 6 months; andCapable and willing to provide written informed consent to this study and unspecified future research for data and donated biospecimens.

Exclusion criteria:Current or recent participation in another research study (e.g., diet or weight loss intervention);Use of medications contraindicating increased consumption of fruits/vegetables (e.g., warfarin);Diagnosis of acute or chronic condition impacting appetite, food intake, and/or the metabolism and absorption of foods to be provided (e.g., Crohn’s disease, celiac disease, ulcerative colitis, short bowel syndrome, chronic diarrhea);Impaired liver or kidney function;Allergies to foods provided in either dietary intervention;Vegetarian, vegan; andFor females: pregnant or lactating or planning to become pregnant during study period.

### Who will take informed consent? {26a}

Interested individuals can contact the study coordinator by phone or email or may follow a QR (quick-response) code/anonymous weblink to obtain more information and complete an eligibility screener via the secure online data collection tool, Research Electronic Data Capture (REDCap) [21, 22]. If they remain interested, individuals complete this screening assessment over the phone, by email, or via REDCap to determine preliminary eligibility based upon self-reported BMI and metabolic syndrome components and other inclusion/exclusion criteria as described above. A waiver of consent for screening allows for collection of contact information at this time. Individuals who are deemed conditionally eligible based upon this screening are contacted via their preferred communication method to schedule an in-person assessment.

After phone/email screening for basic eligibility, an eligibility/enrollment visit is scheduled and potential participants visit the University of Colorado Clinical and Translational Research Center (CTRC). A digital copy (PDF) of the consent form is emailed to participants for review prior to this visit. During the in-person CTRC visit, informed consent is obtained by the study coordinator using the e-Consent framework in REDCap [23]. The consent form is reviewed in a private setting, and potential participants are given the opportunity to ask questions prior to providing consent. Individuals must exhibit understanding by answering questions about the purpose of the study, participation requirements, risks, and benefits before providing informed consent. Those who refuse to provide informed consent at this time are discontinued from participation. Consented participants are registered with the Clinical Trials Office using the OnCore clinical trial management system (Advarra Research, Columbia, MD, USA).

### Additional consent provisions for collection and use of participant data and biological specimens {26b}

All enrolled participants provide blood, urine, and stool samples at the five in-person data collection visits conducted at baseline and intervention weeks 4, 8, 12, and 16. Data are stored and biospecimen samples are banked for unspecified future research.

### Interventions

#### Explanation for the choice of comparators {6b}

As this is a multi-intervention design, each participant serves as his or her own control to evaluate the primary outcome of detection of FSCs in biospecimens after consumption of each dietary intervention and reproducibility over time within an individual.

#### Intervention description {11a}

The dietary interventions are as follows: (1) Mediterranean-amplified (mini-MED) diet, containing 500 kcal/day from Mediterranean target foods: avocado, basil, cherry, chickpea, oat, red bell pepper, walnut, and salmon or lean, unprocessed beef as a protein source, and (2) habitual/Western (Western) diet, containing 500 kcal/day from non-Mediterranean target foods: cheesecake, chocolate frozen yogurt, refined grain bread, sour cream, white potato, and lean, unprocessed beef. Each intervention is 4 weeks, with a 2-week washout after enrollment but prior to initiation of the first dietary intervention (Fig. 1). Furthermore, each intervention is repeated to evaluate reproducibility within individuals over time.

Diets were designed to incorporate target foods identified from previous metabolomics analyses of 100 foods consumed within a completed MED controlled feeding intervention and representing distinct food groups emphasized (mini-MED) or limited (Western) in a MED dietary pattern. Our preliminary data suggest these foods contain FSCs that are detectable in participant biospecimens after consumption (Table 1). Furthermore, we selected foods that are widely accessible and available year-round and in combination will provide adequate energy to achieve 500 kcal/day. Total energy intake of approximately 3500 kcal/week (500 kcal/day) from these foods is provided. During the mini-MED intervention, participants are provided fresh conventionally-grown avocados, basil, red bell peppers, and beef (both ground 90% lean and beef tenderloin); frozen sweet cherries and Atlantic, farm-raised salmon; canned chickpeas; dried basil and old-fashioned oats; and shelled, unsalted walnuts. During the Western intervention, participants are provided New York style cheesecake and regular sour cream, fresh white potato and beef (both ground 90% lean and beef tenderloin), refined grain rolls, and chocolate frozen yogurt bars. Serving sizes and number of servings per week are determined using the US Dietary Guidelines 2020–2025 [24] and serving size information in the United States Department of Agriculture (USDA)-supported food composition database, FoodData Central (Table 2). Dietary interventions are isocaloric and are not designed to fully replace participants’ usual diets; participants are instructed not to change other aspects of their diet aside from accounting for the 500 kcal/day of foods provided. Participants are asked to refrain from consumption of target Western foods when on each mini-MED intervention and vice versa.

**Table 1 Tab1:** Number of food-specific compounds detected in food and plasma for target foods in mini-MED study

Food group	Food	Compounds detected in food	Compounds detected in plasma
*mini-MED target foods*			
Fruit	Cherry	207	30
Fruit/vegetable	Avocado	1446	136
Vegetable	Red bell pepper	283	27
Herb	Basil	204	112
Nut	Walnut	313	23
Legume	Chickpea	41	17
Whole grain	Oat	185	10
Seafood^a^	Salmon	508	143
Lean meat^b^	Beef	276	76
*Western target foods*			
Red meat	Beef	276	76
Starchy vegetable	White potato	19	0
High-fat dairy	Sour cream	271	8
Sweets/dessert	Chocolate frozen yogurt	467	27
Sweets/dessert	Cheesecake^c^	N/A	N/A
Refined grain	Refined grain bread	56	5

Food-specific compounds identified in foods and plasma from the completed MED controlled feeding intervention provide mini-MED and Western target foods for evaluation of reproducibility within the mini-MED intervention

^a^Participants consume salmon as a protein source during the mini-MED salmon arm

^b^Participants consume lean, unprocessed beef as a protein source during the mini-MED beef arm

^c^Cheesecake is included in the target food list for the Western diet but was not included in the original MED controlled feeding intervention and, as a complex food, was not analyzed using metabolomics and thus food-specific compound data are not available (N/A)

**Table 2 Tab2:** Serving size and energy density of target foods provided during the mini-MED study

Food	kcal per 100 g	Serving size	kcal per serving	Form(s)	Servings per week	kcal per week
*mini-MED target foods*						
Cherry	63	½ cup (75 g)	47	Frozen, unsweetened	7	329
Avocado	167	1/3 total (45.3 g)	76	Raw, California	6	456
Red bell pepper	26	½ cup, chopped (74.5 g)	20	Raw	7	140
Basil	23	2 Tbsp	5	Fresh	5	25
	233	1 tsp	2	Dried	Varies	10
Walnut	654	½ oz (14.18 g)	93	“English”	6	558
Chickpea	139	1/3 can (84.3 g)	117	Canned, drained solids	6	702
Oat	379	1/3 cup (27 g)	102	Oats, regular and quick, dry	6	612
Salmon^a^	208	4 oz (113 g)	236	Atlantic, farmed, raw	3	708
Beef^b^	176	4 oz (113 g)	199	Ground, 90% lean meat, 10% fat, raw	2	398
	246	4 oz (113 g)	278	Beef, tenderloin, steak, separable lean and fat, trimmed to 1/8″ fat, choice, raw	1	278
**Total energy intake per week (kcal/week)**						** ~ 3500**
*Western target foods*						
Beef	176	4 oz (113 g)	199	Ground, 90% lean meat, 10% fat, raw	2	398
	246	4 oz (113 g)	278	Beef, tenderloin, steak, separable lean and fat, trimmed to 1/8″ fat, choice, raw	1	278
White potato	77	1 medium potato	164	Potatoes, flesh and skin, raw	5	820
Sour cream	198	1 Tbsp	24	Cream, sour, cultured	7	168
Chocolate frozen yogurt	131	1 cup	228	Frozen yogurts, chocolate	4	912
Cheesecake	321	1/6 of 17 oz cake (80 g)	257	Cake, cheesecake, commercially prepared	2	514
Refined grain bread	321	1 roll	93	Rolls, dinner, sweet	5	465
**Total energy intake per week (kcal/week)**						** ~ 3500**

All serving size and energy density information for target foods and weekly number of servings are outlined for each dietary intervention period. Participants are asked to consume target foods provided during their prescribed arm (e.g., mini-MED or Western) for each dietary intervention period while refraining from consumption of target foods provided in the other arm

^a^Participants consume salmon as a protein source during the mini-MED salmon arm

^b^Participants consume lean, unprocessed beef as a protein source during the mini-MED beef arm

All target foods for both the mini-MED and Western interventions are purchased by study staff at a local grocery chain using a study-specific “pickup” account [25–27]. Briefly, generic foods matching descriptions in nutrient databases (e.g., FoodData Central, https://fdc.nal.usda.gov/) are identified and Universal Product Codes recorded for consistency in ordering across participants and from week to week. Study personnel place weekly grocery orders for participants for pickup at a predefined time at a grocery store at the participant’s preferred location in the Denver, CO, USA, metropolitan area or for delivery to their home. Participants pick up or have groceries delivered at the time and location specified on a weekly basis. Adequacy of the dietary intervention to meet energy and nutrient intakes is assured by stable weight status, which is assessed weekly using a provided body weight scale and monthly during in-person data collection visits.

#### Criteria for discontinuing or modifying allocated interventions {11b}

No modification of the dietary interventions is permitted, and participants are asked to consume all provided study foods in prescribed amounts for the duration of the study. Participants may voluntarily withdraw from this study at any time for any reason. Furthermore, the principal investigator (PI) may decide to suspend a participant’s participation for any reason, (e.g., if he/she/they refuses to participate in any required study procedures, no longer meets study inclusion criteria, or is lost to follow-up).

#### Strategies to improve adherence to interventions {11c}

We recognize the nature of a feeding intervention within a real-world environment may lead to difficulty with adherence. To improve adherence, the study team purchases and provides all foods for participant consumption and provides detailed descriptions of quantities/number of servings of each food to be consumed per week, including ideas for food pairings and basic recipes upon request. Participants receive guidance and basic education for implementing all phases of the dietary interventions and routine support from the study coordinator to assist in identifying facilitators and barriers to adherence with the interventions. The team also provides a weekly checklist to help participants track their consumption of study foods. Study staff are available by phone, text, and/or email for the duration of the study to assist with any issues that may arise in order to identify and respond to barriers to adherence. The continuity of study staff for the duration allows for rapport-building to increase support and provide accountability. Regular dietary assessment via 3-day food logs aids in monitoring adherence with each intervention. Importantly, we do not want nor expect participants to change any other aspects of their habitual diets aside from consumption or avoidance of the mini-MED and Western diet target foods, and therefore we expect this flexibility to improve overall adherence. To improve adherence with data collection, all participants are given a study calendar containing all planned study visits and sampling procedures for each time point upon enrollment. Written and oral instructions are provided to ensure comprehension, and email reminders are sent prior to each in-person visit. Mid-intervention check-in phone calls with the study coordinator are also completed during each dietary intervention period.

#### Relevant concomitant care permitted or prohibited during the trial {11d}

Concomitant medication is permitted if use was stable for at least 6 months prior to study enrollment and remains stable throughout the study. Participants are asked to refrain from consumption of nutritional supplements, herbal supplements, botanical supplements, and pre- or probiotics aside from those prescribed previously by a physician for the duration of the study.

#### Provisions for post-trial care {30}

The study team will arrange medical care for participants if they experience an injury that is caused by this research. However, they are not provided any compensation if they experience harm or injury from participating in the study.

### Outcomes {12}

The primary outcome for this clinical trial is change in the relative abundance of FSCs from beginning to the end of each dietary intervention period in participant plasma samples. Secondary outcomes include detection of FSCs in participant urine samples as well as mean changes in cardiometabolic health indicators (e.g., total cholesterol, LDL cholesterol, HDL cholesterol, triglycerides, insulin, glucose, systolic and diastolic blood pressure), inflammatory markers (e.g., C-reactive protein, interleukin-6, tumor necrosis factor-alpha, alpha-1-acid glycoprotein), and adipokines (e.g., leptin, adiponectin) over each dietary intervention. Exploratory outcomes include changes in diversity and community composition of the gut microbiota over each dietary intervention period.

#### Participant timeline {13}

See Table 3 for the schedule of enrollment, randomization, interventions, and assessments for all study participants.

**Table 3 Tab3:**
[figure not shown]
Schedule of enrollment, interventions, and assessments for mini-MED clinical trial participants

*Abbreviations*: *CTRC*, Clinical and Translational Science Center; *HIPAA*, Health Information Portability and Accountability Act; *BIA*, bioelectrical impedance; *FMV*, first morning void; *ETK*, EnteroTracker®; *ASA24®*, Automated Self-Administered 24-h Dietary Assessment Tool

^*^Order of intervention is randomized

^a^Blood will be processed for outcomes including: food-specific compounds identified through foodomics analyses; cardiometabolic health indicators (total cholesterol, LDL cholesterol, HDL cholesterol, triglycerides, insulin, glucose); inflammatory markers (e.g., C-reactive protein, interleukin-6, tumor necrosis factor-alpha, alpha-1-acid glycoprotein); and adipokines (e.g., leptin, adiponectin). Remaining samples will be stored for unspecified future analyses

^b^FMV spot and 24-h urine samples will be processed to assess putative biomarkers of dietary intake and food-specific compounds identified through foodomics analyses

^c^Stool samples will be assessed for diversity and community composition of the gut microbiota

#### Sample size {14}

Most of our planned analyses use each individual as their own control by looking at the change over each dietary intervention period. This reduces between subject variability compared to a cross-sectional analysis and increases the statistical power at a given sample size. To obtain a reasonable minimum expected effect size for the mean difference divided by the standard deviation of the difference (i.e., Cohen’s *d* effect size), we used our analysis of salmon FSCs [13]. The minimum salmon FSC effect size that passed an FDR adjustment was 0.45. Using a paired *t*-test after consuming the food, a sample size of *N* = 20 was needed to achieve 80% power for this effect size of 0.45 and a Bonferroni multiple testing adjustment for the number of compounds that increased in the preliminary MED data (*N*_compounds_ = 21; *p*-value_adjusted_ = 0.05/21 = 0.0024). We assume a 10% loss to follow-up based on our experience in similar dietary intervention trials and therefore enroll *n* = 22 eligible individuals to have *n* = 20 individuals complete the trial.

We also evaluated the power of *N* = 20 sample size further using the Bonferroni adjustment for the 21 compounds that increased after consumption of the preliminary Mediterranean diet foods (*p*_adj_ = 0.0024) and a stricter adjustment using all 355 compounds that were detected in the MED foods and plasma (*p*_adj_ = 0.05/355 = 0.00014). For both significance thresholds, we achieve power across a range of relevant effect sizes (Fig. 2) including nearly 100% power to detect an effect size of 0.75 (the median effect size for the salmon FSCs that passed the FDR threshold).

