**Fig. 2 Fig2:**
[figure not shown]
Power calculation for mini-MED clinical trial. Power (*y*-axis) for *N* = 20 for a paired *t*-test of the difference between post- and pre-consumption of a food. Power was evaluated over various effect sizes (*x*-axis, mean difference/SD of difference) for three significance thresholds: nominal threshold of 0.05 (yellow), Bonferroni corrected threshold for 21 compounds that increased after consumption in the initial study (*p* = 2.4e − 3), and Bonferroni corrected threshold for 355 compounds that were detected in MED foods and plasma (*p* = 1.4e − 4)

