## Statistical methods

### Statistical methods for primary and secondary outcomes {20a}

Assessment of the primary outcome of change in FSCs will be completed using the intercept of linear mixed effects models (LMMs) with change in FSCs (post–pre) as the outcome and a random intercept to control for repeated measures. Analysis will be stratified by mini-MED and Western interventions since we expect FSCs to increase during the mini-MED arm and to decrease during the Western arm. FSCs that significantly increase during the mini-MED interventions and significantly decrease during the Western interventions will be considered validated. We will adjust for multiple testing using false discovery rate (FDR) for the number of FSCs [37]. We will complete stratified analysis by intervention period to assess reproducibility of FSCs in increase (mini-MED) and decrease (Western). The relationship between cardiometabolic health indicators and diet intervention will be assessed using LMMs similar to that described above. The relationship between cardiometabolic health indicators and FSCs will be assessed using LMMs over all intervention periods with an interaction term for FSCs and diet (i.e., mini-MED, Western) to capture differential effects by diet.

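### The stated power is for one paired test of a rise, but a compound is validated only if a mini-MED increase and a Western decrease are both significant; that joint power is not given and is well below the stated 80% at d = 0.45.

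*Protocol article*

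**What the plan says.** Protocol article, Sample size {14}: the effect size is the mean difference divided by the SD of the difference, taken from earlier salmon compounds. "The minimum salmon FSC effect size that passed an FDR adjustment was 0.45". The threshold is "a Bonferroni multiple testing adjustment for the number of compounds that increased in the preliminary MED data", 0.05/21 = 0.0024. On that basis, "Using a paired *t*-test after consuming the food, a sample size of *N* = 20 was needed to achieve 80% power". The section also considers "a stricter adjustment using all 355 compounds that were detected in the MED foods and plasma" (0.05/355 = 0.00014) and claims close to 100% power at d = 0.75 for both thresholds. The Fig. 2 legend confirms the test: "Power (*y*-axis) for *N* = 20 for a paired *t*-test of the difference between post- and pre-consumption of a food".

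Statistical methods {20a}: the primary analysis tests the intercept of a random-intercept model of change, fitted separately by diet because opposite directions are expected: "Analysis will be stratified by mini-MED and Western interventions since we expect FSCs to increase during the mini-MED arm and to decrease during the Western". The decision rule is: "FSCs that significantly increase during the mini-MED interventions and significantly decrease during the Western interventions will be considered validated". Multiplicity is handled by FDR.

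Trial design {8} and Sequence generation {16a}: each participant has two mini-MED and two Western periods in alternation, and half are randomised to start on Western. Salmon is eaten in one of the two mini-MED periods. Beef is eaten in the other one and in both Western periods.

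**The concern.** Sections {14} and {20a} describe different tests. The first has one change per person and asks only about a rise. The second has two changes per person in each diet and requires two significant results in opposite directions. The chance of passing both cannot exceed the chance of passing the weaker one. The article gives no effect size or power for the Western decrease and none for the two results together.

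The trial's main product is a list of compounds that are validated or not. A reader of {14} will take 80%, or close to 100%, as the chance that a truly responsive compound gets onto the list, and will read a compound left off as a failed biomarker. If the true chance is much lower, being left off says little at the planned minimum effect.

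**Working it through.** **Inputs from the article.** N = 20 completers; d = 0.45 and 0.75; alpha 0.05/21 = 0.00238 and 0.05/355 = 0.00014; two changes per person per diet; half start on Western.

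**Assumptions.** Tests are two-sided (the article does not say). There are 10 participants per starting diet. Visit errors are independent, so the two same-diet changes are uncorrelated. Values are untransformed (the plan ranks them). Bonferroni stands in for FDR. The compound comes from a plant food eaten in both mini-MED periods.

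**Step 1: the plan's own figure.** Paired t-test power = P(T > t[1 − α/2, n − 1]), where T is noncentral t with n − 1 degrees of freedom and noncentrality d√n.

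- n = 20, d = 0.45, alpha 0.05/21: noncentrality 0.45 × √20 = 2.01, power 10.4% (15.5% one-sided). Stated: 80%.
- n = 20, d = 0.75: 46.6% at 0.05/21 and 14.5% at 0.05/355. Stated: close to 100%.
- Smallest n for 80% at d = 0.45, alpha 0.05/21: 79.

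The stated figures do not reproduce even for the test they name.

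**Step 2: one leg of the planned analysis.** With two changes per diet and within-person correlation ρ, the effect on the participant mean is d / √((1 + ρ)/2).

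- ρ = 0: 0.45 × √2 = 0.636, power 30% at 0.05/21.
- ρ = 0.5: 0.45 / √0.75 = 0.520, power 16%.
- Upper bound, 40 independent changes in a plain t-test: 36%.

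Using both changes therefore raises power above the 10.4% of Step 1.

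**Step 3: both legs.** I simulated the five-visit alternating design (SD of one change = 1; 100,000 runs) and tested participant mean changes per diet. In the second scenario Western-first participants, who have had no mini-MED period yet, show no decrease in their first Western period. That affects 10 of the 40 Western changes, so the average Western change is −0.75d.

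| d | alpha | Increase leg | Both legs, full decrease in every Western period | Both legs, no decrease in a first Western period |
|---|---|---|---|---|
| 0.45 | 0.05/21 | 30% | 19% | 9% |
| 0.75 | 0.05/21 | 87% | 80% | 48% |
| 0.75 | 0.05/355 | 52% | 39% | 14% |
| 1.0 | 0.05/21 | 99% | 99% | 82% |
| 0.45 | 0.05, unadjusted | 77% | 68% | 49% |

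In the second scenario 80% joint power at 0.05/21 needs d of about 1.0. With a within-person correlation of 0.5 in place of 0, joint power at 0.05/21 falls further: from 19% to 12% (first scenario) and from 9% to 7% (second) at d = 0.45; from 80% to 58% and from 48% to 41% at d = 0.75.

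**Step 4: what remains once the single-test figure is corrected.** If each leg truly had 80% power and the two were independent, joint power would be 0.8 × 0.8 = 64% (between 60% and 80% under any dependence). In the simulated design, setting d to about 0.70 gives the increase leg 80%; joint power in the second scenario is then about 41%.

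**The case against.** The strongest reply concerns attribution. A reader might infer that the two-leg rule takes power from 80% down to 9% or 19%. The figures do not support that: most of the gap is the single-test arithmetic (80% stated, 10.4% recomputed), and the mixed model with two changes per diet gains power. At d = 0.45 the loss from requiring both legs is from 30% to 19%, or to 9%. This part of the objection stands.

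A second tempting inference is that N = 20 came from counting 20 × 4 = 80 independent changes. Eighty changes do give 80.8% at d = 0.45, and 99.97% and 99.5% at d = 0.75. But the article mentions no such count, and the Fig. 2 legend describes a test "for a paired *t*-test of the difference between post- and pre-consumption of a food", which does not fit Western periods. It remains a guess.

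Third, FDR is more lenient than Bonferroni. That is true, and at d = 0.75 with no adjustment at all joint power is 99% or 91%. At d = 0.45, however, the unadjusted 0.05 level, an upper limit for a 5% FDR, still gives only 68% or 49%.

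Fourth, single-test sizing is common, {8} calls the outcome assessment exploratory, and joint power might appear in an unseen analysis plan. Against this, Objectives {7} makes validation the primary aim and {20a} fixes a pass/fail rule. The point is that {14} and {20a} as published do not match, not that a detail was left out.

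**Conclusion.** The point holds. The power in {14} and Fig. 2 is not the power of the primary rule, and no scenario examined gives 80% at d = 0.45. For a plant-food compound at alpha 0.05/21, joint power is about 19% under the favourable assumption and about 9% when a first Western period shows no decrease; at d = 0.75 the figures are 80% and 48%. With no multiplicity adjustment they are 68% and 49% at d = 0.45.

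The exact values depend on things the article does not give: the within-person correlation, the size of the Western decrease, sidedness, and the effect of ranking. A reader might conclude that N = 20 suffices at d of about 0.75 (or about 0.85 with some within-person correlation). That holds only if every Western period shows a full decrease, which does not fit a design where half the participants start on Western.

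The figures do not carry over to salmon compounds, which can rise in only one mini-MED period, or to beef compounds, for which no Western decrease is expected because beef is also eaten there. The numerical fault in the single-test figure and the mismatch with the rule are distinct: correcting the first leaves the second.

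**What to change.** Keep 22 enrolled. In {14} and Fig. 2:

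1. Replace the stated power with simulated joint power for the {20a} rule under the actual four-period sequences, with no expected decrease in a first Western period, over a stated range of within-person correlation (for example 0 to 0.5).
2. Treat salmon and beef compounds separately from plant-food compounds.
3. State the effect size at which N = 20 gives 80% joint power under those assumptions. Do not adopt 0.75 or 0.85.
4. Label any single-leg power that is kept as 'increase leg only'.

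In reporting, describe a compound that fails either leg as 'not confirmed', and give both leg estimates with confidence intervals.

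The cost is a short simulation and revised wording, with no extra participants. The downside is a less favourable stated power.

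### The powers stated for N = 20 (80% at d = 0.45, nearly 100% at d = 0.75) do not follow from the stated paired t-test, which gives about 10% and 15–47% two-sided

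*Protocol article*

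**What the plan says.** Everything needed is in the protocol article, Sample size {14}, and the legend of Fig. 2.

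- **Effect size:** Cohen's d, defined as "the mean difference divided by the standard deviation of the difference".
- **Minimum effect:** "The minimum salmon FSC effect size that passed an FDR adjustment was 0.45".
- **Claim 1:** with a paired t-test, N = 20 "was needed to achieve 80% power for this effect size of 0.45 and a Bonferroni multiple testing adjustment". The adjustment is over 21 compounds, "0.05/21 = 0.0024".
- **Claim 2:** at this threshold and at a stricter one over 355 compounds, "0.05/355 = 0.00014", power is adequate over the relevant effects, "including nearly 100% power to detect an effect size of 0.75". The value 0.75 is the median effect among the salmon compounds that passed the false discovery rate (FDR) threshold.
- **Fig. 2 legend:** the curves are for N = 20 and "for a paired *t*-test of the difference between post- and pre-consumption of a food", with the same effect definition and thresholds plus an unadjusted 0.05.

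Sidedness is not stated. Twenty-two participants are enrolled so that 20 complete.

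**The concern.** The power of a paired t-test is fixed by the number of pairs, d, alpha and sidedness. With 20 pairs and d = 0.45 the t statistic is expected to fall near 2, while the critical value at 0.0024 is above 3. Power must then be far below one half, so 80% cannot be right. The same reasoning rules out near-certainty at d = 0.75, where the t statistic is expected near 3.4 and the critical values are 3.5 and 4.7.

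At stake is the only numerical justification given for N. Under Statistical methods {20a}, a compound counts as validated only if it rises significantly on mini-MED and falls significantly on Western. A reader who trusts the stated power would take a non-significant compound as fairly strong evidence that it does not respond, and this sample size does not support that inference.

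**Working it through.** **Inputs** (Sample size {14} and Fig. 2 legend): n = 20 pairs; d = 0.45 and 0.75 on the SD of the difference; alpha = 0.05/21 = 0.00238 and 0.05/355 = 0.000141. Sidedness is unstated, so both versions are shown.

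**Formula.** Under the alternative, the paired t statistic is noncentral t with df = n − 1 and noncentrality d√n. Two-sided power = P(|T| > t(1 − alpha/2, n − 1)). For one-sided power, use alpha in place of alpha/2 and the upper tail only.

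**Numbers put in, n = 20, df = 19**

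- Noncentrality: 0.45 × √20 = 2.01; 0.75 × √20 = 3.35.
- Two-sided critical t: 3.50 at 0.05/21; 4.74 at 0.05/355.
- One-sided critical t: 3.20 and 4.44.

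| d | alpha | Stated | Two-sided | One-sided |
|---|---|---|---|---|
| 0.45 | 0.05/21 | 80% | 10.4% | 15.5% |
| 0.75 | 0.05/21 | nearly 100% | 46.6% | 57.2% |
| 0.75 | 0.05/355 | nearly 100% | 14.5% | 20.2% |
| 0.45 | 0.05, unadjusted | – | 48.0% | 61.6% |
| 0.75 | 0.05, unadjusted | – | 88.9% | 94.4% |

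A simulation of 300,000 trials per effect size agrees for the two-sided test: 10.5% for d = 0.45 at 0.05/21, and 46.6% and 14.5% for d = 0.75.

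**Attempts to reproduce the stated figures**

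- *Normal approximation, n = 20.* For d = 0.45 at 0.05/21: 15.3% two-sided, 20.9% one-sided.
- *All 22 enrolled analysed.* For d = 0.45 at 0.05/21: 12.5% two-sided.
- *Both periods of a diet as 40 independent changes (two-sided).* 36.0% for d = 0.45 at 0.05/21; 92.2% and 69.1% for d = 0.75 at the two thresholds.
- *80 independent pairs (two-sided).* 80.8% for d = 0.45 at 0.05/21; 99.97% and 99.5% for d = 0.75. This matches every stated figure.
- *d rescaled to the SD of a single measurement.* 80% for d = 0.45 at 0.05/21 needs a pre–post correlation of about 0.90, and this contradicts the stated definition of d.

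**Pairs needed for 80% power.** For d = 0.45 at 0.05/21: 79 two-sided, 71 one-sided. For d = 0.75, two-sided: 32 at 0.05/21 and 46 at 0.05/355.

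**Effect detectable with 80% power, n = 20, two-sided.** d = 0.99 at 0.05/21 and 1.28 at 0.05/355.

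**Using two periods per diet.** Average each participant's two changes and keep 19 df. The SD of the average is the SD of one change × √((1 + ρ)/2), where ρ is the within-person correlation of the two changes. The documents give no ρ, so 0 to 0.5 is an assumed range. At 0.05/21:

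- ρ = 0: 0.99 × √0.50 = 0.70
- ρ = 0.3: 0.99 × √0.65 = 0.80
- ρ = 0.5: 0.99 × √0.75 = 0.86

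This holds only for foods eaten in both periods of the diet. Salmon is eaten in one mini-MED period per participant (Trial design {8}), so its compounds stay at 0.99.

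**The case against.** The best defence is that the paired t-test is only a planning device. Statistical methods {20a} specifies a linear mixed model on the changes, stratified by diet, with FDR control, and section {20c} ranks the values first. FDR control is no stricter than Bonferroni over the same compounds, and each diet is given twice. The real analysis may therefore have more power than the table shows. Trial design {8} also calls the assessment of outcomes exploratory.

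Much of this stands. A reader might infer that the planned analysis has 10% power, or that most compounds with the minimum effect will miss significance. Neither is shown, because the recomputed values belong to the Bonferroni paired t-test. A reader might also infer that the plan treats a non-significant compound as refuted. It does not: it says only when a compound is considered validated. What does not stand is using the planned analysis to defend the stated figures. They are claimed for a paired t-test at Bonferroni thresholds with N = 20, and at that N even an unadjusted 0.05 does not deliver 80% for d = 0.45.

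The second defence is that 80 pairs reproduces every figure, and 20 participants × 4 periods = 80. That this is the source is conjecture, since the documents do not say so. It would not justify the claim either. The text and the legend say N = 20, and the analysis is stratified by diet, so a stratum holds at most 20 × 2 = 40 changes, two from each person.

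Finally, a reader might conclude that the curves in Fig. 2 are wrong. The figure is not reproduced in the text available for this review, so only its legend can be checked.

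**Conclusion.** The error is confirmed, and it lies in the stated justification of N. Against the stated 80%, the stated test has 10.4% power (15.5% one-sided). Against nearly 100%, it has 46.6% and 14.5% at the two thresholds (57.2% and 20.2% one-sided). The 80% claim needs about four times the pairs: 79/20 = 3.95 two-sided, 71/20 = 3.55 one-sided.

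The conclusion rests only on the document's own N, d, alpha and test. It holds for either sidedness, and the most generous reading of the repeated periods does not reverse it: 40 independent changes still give 36% against 80%, and 69% against nearly 100% at the stricter threshold. It does not show that 22 is an unacceptable enrolment for an exploratory validation study, and it does not quantify the power of the mixed-model analysis with FDR control.

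**What to change.** Keep enrolment and rewrite Sample size {14}:

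1. State whether the tests are one- or two-sided.
2. Replace the 80% figure with 10.4% two-sided (15.5% one-sided) for d = 0.45 at 0.05/21. Remove the near-certainty claim for d = 0.75 and give 46.6% and 14.5% two-sided (57.2% and 20.2% one-sided) at the two thresholds.
3. Give the effect detectable with 80% power at N = 20, two-sided: about 0.99 at 0.05/21 and 1.28 at 0.05/355.
4. If the repeated periods are to be credited, give about 0.70 to 0.86 at 0.05/21 for an assumed within-person correlation of 0 to 0.5. Limit this to foods eaten in both periods of the diet, and say that it does not apply to salmon.
5. Note that these are Bonferroni paired t-test figures and that the planned mixed model with FDR control may have somewhat higher power.
6. Check Fig. 2 against these values and redraw it if it shows the same figures as the text.
7. State that a compound that does not reach significance is inconclusive at this sample size.

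The cost is a paragraph of text and possibly one figure. The stated power becomes much less favourable; enrolment, procedures and the planned analysis do not change.
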